##### Conduct to be followed in the event of signs of TCI

In patients presenting signs of TCI, the lock studied will be maintained and patient management will be implemented according to the decision taken by the physician responsible for the patient in accordance with the practice of each centre. The diagnosis of TCI and its type will be confirmed or not a posteriori by the EAC.

##### Conduct to be followed in the event of catheter dysfunction

At each dialysis session, when extracorporeal blood flow of ≥300 ml/min cannot be achieved with an arterial line pressure higher than − 300 mmHg, the strategy to follow for restoring catheter patency will be to use successively, if necessary, flushing of catheter lumens with saline using a 10 mL syringe, reposition of the patient, reversal of the lines, and fibrinolytic therapy in the absence of contra-indications (administered, for example, at the start of the following dialysis session). The value of blood flow rate and pressure on the arterial line just before each reversal of the lines or fibrinolytic therapy prescription will be noted on the nurse’s record. The time of reversal of the line or fibrinolytic therapy use will be noted on the nurse’s record. Except when a fibrinolytic interdialytic lock is prescribed, the study lock will be maintained.

##### Conduct to be followed in the event of protocol violation

Anticipated violations to study protocol have been described above. Violations not mentioned can be recorded by the CRA as required by the protocol. Any questions regarding protocol violations should be directed to the steering committee (Additional file 1) by phone.

#### Study assessment

At each session, the nurse in charge of the patient will search for signs indicating the presence of a TCI or dysfunction using a check list (comprising clinical signs of infection and bacteriological samples, antibiotic treatment, TC lines inversion and fibrinolytic treatments) according to the usual practice of the dialysis centres and clinical practice guidelines [26, 28]. Data will be collected weekly in an electronic case report form specifically developed for the study. Data for adjudication of the primary outcomes and serious adverse events will be recorded continuously.

#### Coordination and conduct of the trial

Before the start of the study, all health-care workers and clinical research assistants in the 14 participating study centres will attend a formal training session on the study protocol, patient randomization and data collection in the Clinsight Clinical Data Monitoring Software (CDMS) electronic case report form. CDMS is a secure, interactive, web response system available at each study centre. The data manager will have access to the dataset. He will send login with limited access to each investigators ans local clinical research assistant. All documents required for the study will be available in each dialysis centre. Data monitoring in each center will be made by the same coordinating clinical research assistant independent from each study center. The principal investigator and a clinical research assistant will be available to discuss any problem concerning data collection, treatment invoices and protocol compliance and to assess study progress. Informations relative to important protocol modifications will be communicated to investigators using email and CDMS.

#### Interim analysis and independent data and safety monitoring committee

An independent data and safety monitoring committee (Additional file 1) will analyse the adverse events, give its opinion on major amendments of the protocol, proceed to the interpretation of an intermediate analysis (at 1/3 of the inclusions) and if deemed necessary announce the suspension or early termination of the study.

### Sample size calculation

The working hypothesis of this randomized controlled trial is that Ethenox will double the median time to TCI. On the basis of the data collected in DIALIN, median TC duration use is 6 months [29]. The median survival time without TCI reported in recent clinical trials ranges between 690 and 1150 days. However, to achieve a statistical power of 90% with a risk of type I error of 5%, a total of 400 patients need to be enrolled over a period of 24 months.

### Statistical analysis

#### General consideration

The statistical unit of the primary analysis and of most secondary analyses will be the TC. When a new TC is inserted in a patient participating in the study, the new TC will be analysed for the occurrence of a TCI or TC dysfunction only from the time when the patient fulfils the eligibility criteria. This will rule out ongoing TCI or early dysfunction of the TC due to poor positioning at the time of insertion or an anatomical abnormality of the patient.

The principal analysis will be performed on the intention-to-treat principle with Stata software (version13, StataCorp, College Station, TX). The tests will be two-sided, with a type I error set at α = 0.05. Quantitative variables will be presented as mean ± SD when normally distributed (assumption of normality studied by Shapiro-Wilk test), and for non-normal distributions as median, quartiles and range. Qualitative variables will be expressed as numbers and associated percentages.

#### Primary analysis

To evidence the efficacy of the Ethenox lock solution in preventing TCIs in comparison with the reference lock solutions (UFH 5000 U/mL or Citrate 4%), the censored data will be estimated by the Kaplan-Meier method. The comparison between groups regarding the primary endpoint will be performed with a marginal Cox proportional hazard model. Results will be expressed as hazard ratios and 95% confidence interval. Second, owing to the possible non-random censoring process the proposition to right-censor patients at the time of TC removal is debatable. The previous models will be performed with the Inverse Censoring Probability Weighting estimator. Finally, because of possible competing events, which prevent an event of interest from occurring rather than just preventing it from being seen to happen (censoring), Fine and Gray’s approach will be used.

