#### Randomization

Enrolled patients will be randomly assigned in a 1:1 ratio either to the intervention group (Ethenox) or to the control group (reference solution: UFH 5000 U/mL or citrate 4% *w*/*v* depending on the solution instilled in the patient’s TCs prior to inclusion). Random allocation will be performed by minimization using a computer algorithm. Minimization strata will be the study centre, the incident or prevalent nature of the TC and in the prevalent group the existence or not of a previous infection of the TC in place (Fig. 1).

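### The primary Cox model names none of the minimisation factors; stratifying by centre and adjusting for TC status would be a free, modest gain

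*Protocol article*

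**What the plan says.** In the Protocol article, Randomization: "Random allocation will be performed by minimization using a computer algorithm". The factors follow: "Minimization strata will be the study centre, the incident or prevalent nature of the TC" and, third, "in the prevalent group the existence or not of a previous infection of the TC in place".

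Under Primary analysis: "The comparison between groups regarding the primary endpoint will be performed with a marginal Cox proportional hazard model". Results are to be given as hazard ratios with 95% confidence intervals, followed by a censoring-weighted version and a Fine-Gray version. No covariate or stratum is named for any of the three, and none is ruled out.

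Under General consideration: "The statistical unit of the primary analysis and of most secondary analyses will be the TC", so one patient can contribute several TCs. The same section states: "The tests will be two-sided, with a type I error set at α = 0.05".

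Under Secondary analysis, model terms are listed for longitudinal data: group, time and their interaction as fixed effects, and patient as a random effect. The minimisation factors are not among them. Patient-level comparisons use two-sample tests that take no covariates.

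**The concern.** Minimisation makes the arms more alike on its factors than simple randomisation would. If a factor predicts infection, the treatment estimate then varies less from trial to trial than an unadjusted model assumes. The model-based standard error is too large, the confidence interval too wide and the test conservative. In a Cox model, leaving out prognostic factors also moves the marginal HR towards 1 relative to the conditional HR, which costs some further power.

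The documents make a centre effect plausible without giving a size. Catheter handling follows each centre's own protocol, each centre picks its antiseptic, and suspected infection is managed by local practice. Minimising on previous infection suggests that the authors regard it as relevant to risk. At stake is a modest amount of power, plus the choice between adjusted and unadjusted results, which is better fixed in advance.

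**Working it through.** **1. The plan's own figure.** Inputs from Sample size calculation: two-sided 5%, power 90%, "Ethenox will double the median time to TCI" (HR 0.5 under exponential times), control median 690 days (lower end of the stated range), 400 patients. Follow-up of up to 12 months is from Design and setting of the study.

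- Schoenfeld events: 4 × (1.960 + 1.282)² / (ln 2)² = 4 × 10.507 / 0.4805 = 87.5, so 88.
- Freedman events: [(1 + 0.5)/(1 − 0.5)]² × 10.507 = 94.6, so 95.
- Mean event probability over 365 days: control 1 − 2^(−365/690) = 0.307; treated 1 − 2^(−365/1380) = 0.168; mean 0.237. Freedman N = 401.
- Over 335 days the mean probability is 0.220. Schoenfeld N = 400.

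The stated 400 is therefore reproduced by a plain two-group comparison without adjustment and without censoring at TC removal. That gives about 88 to 95 events, or 6 to 7 per centre across the 14 centres.

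**2. Effect of leaving the factors out.** Simulation: 400 patients, 14 centres, biased-coin minimisation (probability 0.85, assumed) on centre and three-level TC status, 12 months, 690-day control median, one TC per patient, model-based standard error, 2,500 trials per setting. The adjusted model has TC status and centre as covariates. Prognostic strengths are assumptions: HR for previous infection, HR for incident TC, SD of centre log hazards.

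| Assumed strength | Null rejection, unadjusted / adjusted | Power at HR 0.5, unadjusted / adjusted | Power difference |
|---|---|---|---|
| None (1, 1, 0) | 0.045 / 0.052 | 0.910 / 0.917 | 0.7 points |
| Weak (1.5, 1.2, 0.3) | 0.040 / 0.048 | 0.901 / 0.913 | 1.2 points |
| Moderate (2, 1.3, 0.5) | 0.042 / 0.059 | 0.888 / 0.913 | 2.5 points |
| Strong (3, 1.5, 0.7) | 0.038 / 0.060 | 0.846 / 0.894 | 4.8 points |

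Monte Carlo standard errors are about √(0.05 × 0.95/2500) = 0.4 points for null rejection and √(0.9 × 0.1/2500) = 0.6 points for power. The first row is compatible with no difference.

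**3. The mechanism.** Under the null, the unadjusted model SE against the true SD of the log HR is 0.185 against 0.179 (moderate) and 0.190 against 0.178 (strong).

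- Moderate: 1.96 × 0.185/0.179 = 2.03, a two-sided level of about 4.3%.
- Strong: 1.96 × 0.190/0.178 = 2.09, about 3.6%.

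These agree with the simulated 4.2% and 3.8%.

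**4. Form of adjustment.** Centre dummies are not the best choice. They gave null rejection up to 0.060, so part of the gain in the table is not real. In the strong setting 54 (null) and 50 (HR 0.5) of the 2,500 adjusted fits gave no usable estimate. Stratifying the baseline hazard behaves better:

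- Allocation balanced within strata, test stratified by centre and previous infection, 1,200 trials. Centre SD 0.5 and previous-infection HR 2: null rejection 3.9% unadjusted and 5.0% stratified, power 88% and 89%. SD 0.8 and HR 3: 3.3% and 5.1%, power 82% and 86%.
- Biased-coin minimisation, Cox model stratified by centre with TC status as covariates. Moderate strength: 4.2% and 5.1%, power 89% and 90%. Strong: 2.7% and 5.4%, power 80% and 86%. With non-prognostic factors there was no gain and no material loss. The exact strengths of this run are not tabulated here, so it serves mainly to confirm the direction.

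**5. The hazard ratios.** With a true conditional HR of 0.50, SD 0.8 and HR 3, the unadjusted estimate was 0.53 and the stratified one 0.50. The HR is non-collapsible: these are two different quantities, each estimated properly.

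**The case against.** The strongest objection is that silence is not exclusion. This is a condensed article, the SAP is not shown, and a covariate list is commonly left to it. The word marginal fits the clustering of TCs within patients and is compatible with covariates or strata. A reader might infer that the plan deliberately leaves the factors out; no section says so, and that part of the objection stands. What remains is that the model as described is an unadjusted one, and the factors are also absent where Secondary analysis does list model terms. The sample size matches an unadjusted comparison too, though that is weak evidence, since sample sizes are often computed that way.

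Second, the loss depends on prognostic strengths that the documents do not give. This stands as well. With no effect the difference is within simulation error, and unadjusted power stays within 2 points of 90% in the weak and moderate settings.

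Third, the simulations use one TC per patient and a model-based standard error, whereas the trial may have several TCs per patient and would need a clustered variance. The figures are therefore indicative. Clustering by patient deals with repeated TCs but takes no account of the forced balance on centre and TC status, so the direction should hold.

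Fourth, adjustment is not quite cost-free. Centre dummies distort the test slightly, and TCs inserted after randomisation have no minimisation value of their own. Both are fair, and the fix below addresses them.

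**Conclusion.** The point holds as a free improvement. If the primary model is fitted as described and the factors are prognostic, the test rejects at about 3–4% under the null rather than 5%. It gives up about 0 to 5 points of power: around 1 to 2.5 at moderate strength, and 4 to 6 only under strong assumed effects. These sizes rest on assumed prognostic strengths, the 690-day median, 12 months of follow-up and one TC per patient.

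Three stronger readings are tempting and not supported. The result would not be invalid: the error is on the safe side, so a positive finding would stand. The unadjusted HR would not be biased; it is a marginal effect. And a loss of power is not certain, because it depends on figures that the documents do not give. Whether 400 patients yield enough events at longer medians or with censoring at TC removal is a separate question.

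**What to change.** Specify the primary marginal Cox model with:

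- baseline hazard stratified by centre, with small centres pooled by a rule set before unblinding;
- a three-level TC status covariate (incident; prevalent without previous infection; prevalent with previous infection), fixed at the patient's value at randomisation for all of that patient's TCs;
- patient-clustered robust variance.

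Use the same terms in the censoring-weighted and Fine-Gray analyses, and report the unadjusted HR as supportive. If the SAP already says this, a sentence in the protocol pointing to it is enough.

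The cost is wording and a pooling rule. All the factors are known at randomisation, so no extra data or patients are needed. Little is lost if the factors turn out not to be prognostic.

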#### Secondary analysis

For the secondary endpoint, the censored data will be estimated by the Kaplan-Meier method and compared between groups by a marginal Cox proportional hazard model. Concerning the parameters collected longitudinally, mixed models will be performed to take into account inter- and intra-patient variability. The effects of group, time and their interaction (time x group) will be studied as fixed effects, with the patient effect considered as a random effect (data repeated for the same subject). Lastly, regarding comparisons for which the statistical unit will be the patient, the usual tests will be applied: Student t-test or Mann-Whitney test if the conditions of the t-test are not competed (normality, homoscedasticity studied by the Fisher-Snedecor test) for parameters of a quantitative nature and the Chi-squared test or Fisher’s exact test for categorical variables.

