### Design and setting of the study

ETERNITY is a prospective phase III multi-centre, single blind, randomized, controlled, parallel group study (Fig. 1). It will be carried out in 14 dialysis units in France (Additional file 2). The planned duration of the study will be 36 months. The enrolment period will be 24 months. Patients will receive the study treatment for up to 12 months or until 1 month before the end of the study. To evaluate safety, all the patients included will be followed for adverse events for 4 additional weeks after they have received their last treatment dose in the study (Fig. 2).

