**Fig. 2 Fig2:**
[figure not shown]
Scheme of participation in the study for a patient. TC is the statististical unit and several consecutive TC will be analysed in a same patient from the time the inclusion criteria are fullfilled

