#### Secondary endpoints

Secondary endpoints will comprise:Other TCI prevention criteriaTime to first definitive or probable TCBSITime to first ESIIncidence rate of definitive or probable TCBSIIncidence rate of ESIPrevention of TC colonizations: rates of colonization of removed TCsCatheter patencyTime to first TC dysfunctionIncidence rate of TC dysfunctionsDialysis dose: monthly (Kt/V)_sp_ and (KT/V)_e_ (2nd generation Daugirdas equation) and Kt/V measured by the dialysis machine (ionic dialysance or optical measurement of urea in the effluent dialysate)TC survival: time to TC removalHealth care consumptionTime to first systemic antibiotic treatment for TCITotal duration and type of antibiotic treatmentTime to first hospitalization for TCITotal duration of hospital stays for TCITotal number of TCs replaced during the studySafetyIncidence rate of breaches in TC integrity (TC leakage or disruption)Incidence rate of clinical adverse events related to ethanol exposure (tiredness, ethanol taste, headaches, dizziness, nausea, light-headedness, and increase in serum aspartate aminotransferase, alanine aminotransferase, gamma-glutamyl transferase or alkaline phosphatase).Incidence rate of type II heparin-induced thrombocytopenia.Incidence rate of haemorrhages: bleeding or suspected bleeding, qualified as major if associated with a decrease in haemoglobin levels of more than 2 g/dL or the need to transfuse at least two units of red blood cells.Overall mortality: time to death from any causeInflammation: CRP value (measured every 3 months).

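### With the patient as the only random effect named, the time-by-group test for Kt/V and CRP can exceed its nominal 5% if time is linear; patient-clustered robust standard errors would prevent this

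*Protocol article*

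**What the plan says.** All of this is in the protocol article.

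- **Model.** Under Secondary analysis, for parameters collected longitudinally, "mixed models will be performed to take into account inter- and intra-patient variability". The fixed part follows: "The effects of group, time and their interaction (time x group) will be studied as fixed effects". The random part is given as "with the patient effect considered as a random effect (data repeated for the same subject". No other random term and no residual correlation is named. Time is not said to be linear or categorical.
- **Error rate.** Under General consideration: "The tests will be two-sided, with a type I error set at α = 0.05".
- **Endpoints.** Secondary endpoints lists dialysis dose under catheter patency, as monthly single-pool and equilibrated Kt/V plus the Kt/V measured by the machine. It also lists inflammation: "CRP value (measured every 3 months".
- **Follow-up and size.** Design and setting: "Patients will receive the study treatment for up to 12 months or until 1 month before the end of the study". Sample size calculation: "a total of 400 patients need to be enrolled over a period of 24 months".
- **Catheters within a patient.** The Fig. 2 legend says that "several consecutive TC will be analysed in a same patient", and the sample size section gives a median catheter use of 6 months.

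**The concern.** A random patient intercept with otherwise independent errors treats any two visits of a patient as equally correlated, whether 1 or 11 months apart. With linear time it also assumes that patients within an arm share one slope.

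The trial's own design gives reason to doubt this. Median catheter use is 6 months and treatment lasts up to 12, so a change of catheter during follow-up is an expected event. Kt/V is used as a patency measure, so its values may cluster within a catheter. Monthly values may also be serially correlated, and patients may differ in slope. The model counts all such variation as independent noise, so the standard error of the interaction comes out too small.

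At stake is the reading of three Kt/V measures and CRP. The Background reports more catheter dysfunction with an earlier ethanol lock, so whether dialysis dose is maintained under Ethenox matters. A chance difference in course, in either direction, could be taken for an effect of the lock.

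**Working it through.** **Inputs from the article:** two-sided alpha 0.05; 400 patients allocated 1:1, so 200 per arm; up to 12 months of treatment, hence about 12 Kt/V values and 4 or 5 CRP values; median catheter use 6 months.

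**Assumed inputs, because the article gives none:** linear time (categorical time is checked at the end), residual SD 0.15 for Kt/V, slope SD, first-order autocorrelation between successive visits, catheter-level SD, and complete follow-up.

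**Formula.** Let c be the centred visit times, Sxx = c'c, n the number of visits, V the true within-patient covariance and M the centring matrix.

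- True variance of a patient's fitted slope: c'Vc / Sxx².
- Variance that the random-intercept model attributes to it: s² / Sxx, with s² = trace(MV)/(n - 1).
- Ratio R = (c'Vc / Sxx) / s².
- Size of the nominal 5% test with no group effect: 2Φ(-1.96/√R).

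R does not depend on the number of patients, so a larger trial does not remove the problem.

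**The plan's own 5%.** With no slope variation and independent residuals, R = 1 and the size is 5.0%.

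**Varying slopes, Kt/V, 12 visits.** With slope SD τ and residual SD σ, R = (1 + k)/(1 + k/11), where k = τ²Sxx/σ² and Sxx = 143. For τ = 0.010: k = 0.0001 × 143/0.0225 = 0.636, R = 1.636/1.058 = 1.55, size 11.5%.

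| Slope SD per month | R | Size |
|---|---|---|
| 0.005 | 1.14 | 6.7% |
| 0.010 | 1.55 | 11.5% |
| 0.015 | 2.15 | 18.1% |
| 0.020 | 2.88 | 24.8% |

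**Autocorrelation between successive visits.**

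| Autocorrelation | Kt/V, 12 values | CRP, 5 values | CRP, 4 values |
|---|---|---|---|
| 0.1 | 7.1% | 6.5% | 6.2% |
| 0.3 | 12.9% | 9.9% | 8.7% |
| 0.5 | 20.8% | 13.6% | 11.3% |
| 0.8 | 35.3% | 19.1% | 14.9% |

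At autocorrelation 0.5, R for Kt/V is 2.42, so the true standard error is √2.42 = 1.56 times the one reported.

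**Catheter clustering, Kt/V.** Exponential catheter durations with a 6-month median give a shared component with correlation exp(-(ln 2/6) × months apart). With residual SD 0.15, a catheter-level SD of 0.10 gives R = 1.61 and size 12.3%; 0.15 gives R = 2.17 and 18.4%.

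**Categorical time.** Here the interaction is a joint test on n - 1 degrees of freedom. At autocorrelation 0.3, 0.5 and 0.8 its size is 6.1%, 7.8% and 11.4% for 12 Kt/V values, 5.5%, 6.2% and 7.4% for five CRP values, and 5.3%, 5.7% and 6.6% for four.

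**Simulation check.** In 1,000 simulated trials per setting with a REML random-intercept fit and 200 patients per arm, slope SDs of 0, 0.010 and 0.020 gave 5.0%, 11.4% and 24.0%, and autocorrelations of 0.5 and 0.8 gave 19.6% and 34.9%. Cutting follow-up with a 6-month median changed the slope results little (4.7%, 12.0% and 26.1%). Patient-clustered robust standard errors on the same fits gave 4.1-6.3%.

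**The case against.** The strongest reply is that this is a condensed article. The sentence says neither that the patient effect is the only random term nor that it is an intercept, and covariance structure and time coding are usual content of an analysis plan that is not shown. That stands as far as missing detail goes: silence on these items is no error. But the article does more than stay silent. It writes out the model, fixed and random parts, and an analyst who follows it as written would fit a random intercept.

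A reader might infer that these tests will reject at 12-35% instead of 5%. The documents do not support that. They give no slope variance, autocorrelation or catheter-level variance, and with none of these the size is 5%. The 35% needs linear time and autocorrelation 0.8 in monthly Kt/V. It does not carry over to CRP, where random slopes alone cannot push the size above 33% with five values or 26% with four. With categorical time there is no common slope to assume, and the excess is small.

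It is also fair to say that persistence of low Kt/V is not documented. The section on catheter dysfunction prescribes stepwise restoration of patency, which may limit it. That argues for showing a range rather than for ignoring the point.

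**Conclusion.** The point holds in conditional form. Fitted as a random intercept with linear time, the named model gives a time-by-group test that is anti-conservative whenever slopes vary, visits are serially correlated or values cluster within catheters. The size runs from 5%, where all of these are absent, to about 25% (slopes) or 35% (autocorrelation) for Kt/V, and to about 19% (autocorrelation) for CRP, over the assumed values tried. How far the trial would depart from 5% cannot be told from the article. An unseen analysis plan may already contain the protection.

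Only secondary endpoints are affected. The primary time-to-infection comparison uses a marginal Cox model and is untouched. The change is worth making because it is simple and protects under all the structures considered.

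**What to change.** In Secondary analysis, add that group and time-by-group in the longitudinal models are tested with patient-clustered robust standard errors. With 400 patients there are ample clusters, and in the simulations this alone brought the size back to about 4-6%.

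Optionally, add a random slope per patient if time is linear, or a catheter-within-patient random effect. With only four or five CRP values the richer structure may be weakly identified, so it should not replace the robust standard errors.

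The cost is one sentence and somewhat wider intervals where slopes or catheters do vary. No data collection or design element changes.
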